# The impact of community health worker-led home delivery of antiretroviral therapy on virological suppression: a non-inferiority cluster-randomized health systems trial in Dar es Salaam, Tanzania

**DOI:** 10.1186/s12913-017-2032-7

**Published:** 2017-02-22

**Keywords:** Antiretroviral therapy, HIV, Community health workers, Nutrition counseling, Food production, Adherence, Retention, Healthcare expenditure

## Abstract

**Background:**

Home delivery of antiretroviral therapy (ART) by community health workers (CHWs) may improve ART retention by reducing the time burden and out-of-pocket expenditures to regularly attend an ART clinic. In addition, ART home delivery may shorten waiting times and improve quality of care for those in facility-based care by decongesting ART clinics. This trial aims to determine whether ART home delivery for patients who are clinically stable on ART combined with facility-based care for those who are not stable on ART is non-inferior to the standard of care (facility-based care for all ART patients) in achieving and maintaining virological suppression.

**Methods:**

This is a non-inferiority cluster-randomized trial set in Dar es Salaam, Tanzania. A cluster is one of 48 healthcare facilities with its surrounding catchment area. 24 clusters were randomized to ART home delivery and 24 to the standard of care. The intervention consists of home visits by CHWs to provide counseling and deliver ART to patients who are stable on ART, while the control is the standard of care (facility-based ART and CHW home visits without ART home delivery). In addition, half of the healthcare facilities in each study arm were randomized to standard counseling during home visits (covering family planning, prevention of HIV transmission, and ART adherence), and half to standard plus nutrition counseling (covering food production and dietary advice). The non-inferiority design applies to the endpoints of the ART home delivery trial; the primary endpoint is the proportion of ART patients at a healthcare facility who are virally suppressed at the end of the study period. The margin of non-inferiority for this primary endpoint was set at nine percentage points.

**Discussion:**

As the number of ART patients in sub-Saharan Africa is expected to rise, this trial provides causal evidence on the effectiveness of a home-based care model that could decongest ART clinics and reduce patients’ healthcare expenditures. More broadly, this trial will inform the increasing policy interest in task-shifting of chronic disease care from facility- to community-based healthcare workers.

**Trial registration:**

ClinicalTrials.gov: NCT02711293. Registration date: 16 March 2016.

**Electronic supplementary material:**

The online version of this article (doi:10.1186/s12913-017-2032-7) contains supplementary material, which is available to authorized users.

## Background

An estimated 37% of the 24.7 million people living with the human immunodeficiency virus (HIV) in sub-Saharan Africa (SSA) were receiving antiretroviral therapy (ART) in 2015 [1, 2]. Since the advent of antiretroviral drugs, the World Health Organization (WHO) has gradually increased the recommended threshold for ART initiation from a CD4-cell count of less than 200 cells/μL in 2006 [3], to less than 350 cells/μL in 2010 [4], and less than 500 cells/μL in 2013 [5]. Most recently, in 2015, the WHO has recommended immediate ART for all people living with HIV, irrespective of CD4 count [6]. As countries expand ART eligibility– and because ART increases the life expectancy of people living with HIV – the number of people needing ART in SSA is likely to increase substantially over the coming decades [6, 7]. However, the financial, human and physical resources available to deliver ART are unlikely to grow in proportion to this increase. These developments call for new models of care that increase the capacity and efficiency of delivering ART without reducing quality of care [8].

### The importance of ART retention and adherence

The benefits from the scale-up in ART coverage will critically depend on life-long ART retention and adherence. A meta-analysis pooling ART adherence data from over 30,000 adult patients in 84 observational studies across 20 countries found that 38% of patients took less than 90% of prescribed ART doses [9]. Similarly, previous analyses by our team in a cohort of over 44,000 patients in Dar es Salaam’s adult HIV treatment and care program have found low ART retention and adherence. More specifically, we found that 39% of adults on ART were lost to follow-up within 12 months of initiation (unpublished data). In addition, 19% were non-adherent to ART [10] (as defined by non-compliance with scheduled ART pickup visits of greater than 5%) at any given point in time, with the risk of non-adherence increasing with duration on ART. Worryingly, the risk of non-adherence also rose independently with increasing calendar year, with the relative risk (RR) of non-adherence being 2.0 (95% confidence interval: 1.9-2.1) in 2010 compared to the reference year 2004. Poor adherence is not only likely to lead to treatment failure and resulting morbidity and mortality, but also increases the risk of HIV transmission and, crucially, the development of resistant HIV strains [11–13]. Increasing ART resistance may narrow future antiretroviral drug options, and thus reduce ART access and increase the cost of effective HIV treatment as programs have to move to more expensive second and third-line regimens.

### Reasons for community health worker-led home delivery of ART to improve retention and adherence

In a large qualitative study in three urban settings in sub-Saharan Africa, including Dar es Salaam, Ware et al. found that the main unintentional reason for missed ART clinic visits was a lack of time due to other, often unexpected, events in a patient’s life [14]. In addition, many studies have identified the cost to patients of attending ART clinics (not just expenses on user fees but also on transport, food, and lost income [14–18]), transport-related factors [19], and long clinic waiting times [14] as being important barriers to ART retention. Given that the delivery of ART at home through community health workers (CHWs) would overcome many of these barriers, CHWs have the potential to significantly improve ART retention and adherence.

An additional benefit of a home-based approach to ART arises from the resulting reduced patient load at ART clinics, which may decrease waiting times and improve quality of care as facility-based healthcare workers have more time available per patient. The home delivery of ART by CHWs is, therefore, not merely an intervention aimed at improving ART retention and adherence but also a measure that can shift care from more highly to less well-trained health workers. Such task-shifting measures may therefore alleviate the severe shortage of human resources for health in SSA, which is a central barrier to attaining universal coverage of HIV services [20, 21]. The WHO has identified 313 tasks, which are essential for the prevention of HIV transmission, identification of HIV-infected individuals, provision of basic HIV-related clinical management, and initiation and maintenance of patients on ART. The WHO recommends that 115 of these tasks, including the dispensing of ART, can be performed by CHWs, highlighting the immense potential of task-shifting for HIV-related care [22].

### The current evidence base for home delivery of ART by community health workers

A systematic review of health service delivery for ART provision identified two randomized trials, which evaluated ART home-delivery programs [23]. Both of these trials randomized geographical areas around one ART clinic. The first trial was set in rural Uganda and randomized areas to either home delivery of ART by field officers, or standard facility-based ART [24]. The participants were patients newly initiated on ART. The trial found no difference between study arms in the rate of virological failure or mortality, neither after six months [24] nor at 36-months follow-up [25]. The median expense to patients in terms of transport costs, food, child care, and lost work time due to ART utilization was higher in the facility-based group than in the home-based group at US$60 versus US$29 in the first year, and US$54 versus US$18 in subsequent years. In addition, the median cost to the health system per patient per year was somewhat lower in the CHW group (US$793) than in the facility-based group (US$838) as the increased transport costs for CHWs were offset by patients’ reduced clinic attendance. In another study, the same cohort of patients receiving ART home delivery was compared with ART patients who attended a physician-staffed hospital in an urban sub-district of Uganda [26, 27]. While comparability of the two cohorts is limited by the observational study design, the study found that community-based participants were more likely to achieve viral suppression (after adjusting for CD4-count at baseline and socio-demographic characteristics), and there was no difference in all-cause mortality. The second randomized trial was carried out in rural Kenya and, similar to the Uganda study, found no difference in the percentage of patients with an undetectable viral load, mean CD4-count, incidence of opportunistic infections, and change in ART regimen between stable ART patients who received ART from CHWs during home visits, as compared to patients randomized to standard facility-based ART [28].

This trial differs in several crucial aspects from the two studies described above. Firstly, this trial is the first to evaluate ART home delivery in an urban setting. Secondly, this is a health systems trial, which implements the intervention directly into the routine healthcare system. Both the Uganda and Kenya trial randomized geographic areas around one clinic run by a non-governmental organization [24, 28], while this study is being implemented at all healthcare facilities in Dar es Salaam that offer ART and have an affiliated team of public-sector CHWs. In addition, while the Uganda trial trained a new cadre of field officers to deliver ART by motorbike and the Kenya trial trained ART patients at the clinic to act as community care coordinators, this trial is utilizing a large existing public-sector CHW program in Dar es Salaam. Thirdly, this trial includes a large number (24) of healthcare facilities in each study arm, while both the Uganda and Kenya trial implemented the intervention at only one clinic. Aside from external validity concerns arising from a study carried out in a single clinic, an important disadvantage of drawing the intervention and control group from the same healthcare facility is that ART home delivery is likely to have affected the care provided to the control group, as the shifting of patients to community-based care substantially reduced the patient volume at the facility. Such shifts may have resulted in the control group being a poor counterfactual. Finally, both the Uganda and Kenya trial were unable to rigorously assess the effect of shifting patients to the community on routine facility-based ART. This trial, on the other hand, will be able to compare patient satisfaction, time spent by nurses and physicians with ART patients, and clinicians’ job satisfaction between the 24 intervention and 24 control facilities.

This non-inferiority cluster-randomized trial evaluates the feasibility and effectiveness of CHW-led home delivery of ART in the public-sector healthcare system of Dar es Salaam, the largest city in Eastern Africa. More specifically, this study aims to determine whether a differentiated ART care model (ART home delivery for patients who are clinically stable on ART and standard facility-based care for those who are not stable on ART) is non-inferior to the standard of care (facility-based care for all ART patients) in achieving and maintaining virological suppression.

## Methods/design

### Study setting

The study will be implemented in all three municipalities (Ilala, Kinondoni, and Temeke) of the Dar es Salaam region of Tanzania, which contains the city of Dar es Salaam. The average household size in the Dar es Salaam region is 4.0 people and is virtually the same across its three municipalities (ranging from 3.9 to 4.0). Dar es Salaam’s HIV prevalence was 6.9% among adults aged 15–49 years in 2012, which is above the national prevalence of 5.1% [29].

#### The home-based carer program

This trial utilizes an existing and long-standing public-sector CHW cadre, called home-based carers or HBCs, to deliver the intervention. The CHWs are employed by Dar es Salaam’s municipalities and receive a stipend of 80,000 Tanzanian shilling (approximately equal to 36 US dollars) per month. They are lay healthcare workers whose main responsibility is to conduct regular home visits (at least once every three months) to all households in the neighborhood to which they have been assigned. The precise tasks of the CHWs during these home visits have varied somewhat over the years but generally consist of the provision of information and counseling on a wide variety of health topics, referral of ill clients to healthcare facilities, and promotion of preventive healthcare services. The CHW program exists in most but not all areas of Dar es Salaam. In those areas where the CHW program has been implemented, each neighborhood has one to three CHWs. The CHWs are residents in the neighborhoods in which they work.

### Study duration

Enrolment into the trial took place in facilities in the Temeke municipality from February 29^th^ 2016 to July 29^th^ 2016. Because the number of participants enrolled in Temeke was lower than expected, the trial was expanded to 16 healthcare facilities in the Kinondoni municipality and 14 facilities in the Ilala municipality. Enrolment in Kinondoni took place from August 1^st^ 2016 to November 11^th^ 2016, and enrolment in Ilala from November 14^th^ 2016 to January 20^th^ 2017. The study activities during the trial period are detailed in Fig. 1.

**Fig. 1 Fig1:**
[figure not shown]
Trial activities over the study period

### Eligibility criteria

The eligibility criteria for participants in this trial are: 1) being aged 18 years or older; 2) attending one of the participating healthcare facilities for ART during the enrolment period; and 3) living in a neighborhood in the facility’s catchment area. An additional eligibility criterion for ART home delivery is being clinically stable on ART. A patient is clinically stable on ART if the patient’s most current viral load has been taken less than 12 months prior to enrolment and showed viral suppression. If a viral load measurement is unavailable at the time of enrolment but a CD4-cell count taken in the 12 months prior to enrolment is available, then a patient is clinically stable on ART if the most current CD4-cell count is >350 cells/μL. If neither a viral load nor a CD4-count taken in the 12 months prior to enrolment is available, then a venous blood sample will be taken for a viral load measurement and the result used for the eligibility assessment. Additional requirements for being stable on ART are 1) taking ART for at least six months, and 2) having had a CD4-cell count >350 cells/μL or a suppressed viral load at six or more months after ART initiation. Patients who are pregnant at the time of enrolment (by patient self-report) or unable to provide written informed consent (e.g., due to mental incapacity) are excluded from eligibility.

### Study design

#### Rationale for a non-inferiority design and margin of non-inferiority

The non-inferiority design only applies to the primary endpoint (the proportion of participants with a suppressed HIV viral load). This design choice was made because in settings with an existing CHW program, such as in Dar es Salaam, CHW-led home delivery should likely be the standard of care if it does not negatively affect patients’ health outcomes as compared to standard facility-based care. Two virtually certain benefits of CHW-led ART home delivery are a reduction in 1) patient volume at healthcare facilities, which helps to alleviate the severe shortage of skilled healthcare workers in sub-Saharan Africa [20], and 2) the substantial time and financial (e.g., transport costs) burden on patients of having to attend an ART facility [24, 30]. The main drawback of CHW-led ART home delivery is the cost of establishing and running the CHW program, and the risk of overburdening CHWs, which may lead to a reduction in quality and/or quantity of care for non-ART patients. We would argue that in the case of Dar es Salaam, the cost consideration is minor as the CHW program already exists and is likely continue to run independently of whether CHWs are tasked with ART home delivery. Regarding overburdening CHWs, we carefully monitor the number of visits made by CHWs to non-HIV patients in each study arm and also ascertain CHWs’ job satisfaction and perception of the intervention through semi-structured qualitative interviews.

Based on our own judgement of what constitutes non-inferiority for this intervention and in line with the margin of equivalence of nine percentage points used by Jaffar et al. in their randomized trial of ART home delivery in rural Uganda [24], we chose a margin of non-inferiority of nine percentage points.

#### Randomization

The unit of randomization is a healthcare facility with its surrounding catchment area (Fig. 2). Which healthcare facilities were included in this study was determined by the supervisory structure of CHWs in the routine public-sector health system. Each CHW is supervised by one community outreach nurse who is a nurse based at a healthcare facility. Each community outreach nurse supervises between three and 16 CHWs who work in neighborhoods (*mtaa* in Kiswahili) in the facility’s catchment area. We included all healthcare facilities in Dar es Salaam in this trial, which provide ART and had a community outreach nurse (and thus a team of affiliated CHWs) with the exception of two facilities (Amana Hospital and Mwananyamala District Hospital) because of a conflict with a clinical trial taking place at these facilities. Table 1 describes the characteristics of each cluster.

**Fig. 2 Fig2:**
[figure not shown]
Randomization scheme

**Table 1 Tab1:** Characteristics of the clusters

Name of healthcare facility	Counseling package^a^	Type of healthcare facility	Municipality	No. of patients currently on ART	No. of CHWs in cluster
ART home delivery					
1. Mbagala Rangi Tatu	Standard + nutrition	Hospital	Temeke	15,663	3
2. Tambukareli	Standard	Dispensary	Temeke	1,554	12
3. Yombo Makangarawe	Standard	Dispensary	Temeke	544	2
4. Toa Ngoma	Standard + nutrition	Dispensary	Temeke	239	12
5. Buza	Standard + nutrition	Dispensary	Temeke	215	5
6. Arafa Ugweno	Standard	Dispensary	Temeke	202	3
7. Mji mwema	Standard	Dispensary	Temeke	161	8
8. Kimbiji	Standard + nutrition	Dispensary	Temeke	119	6
9. Keko	Standard + nutrition	Dispensary	Temeke	79	4
10. Tandale	Standard	Dispensary	Kinondoni	2,951	9
11. Mburahati	Standard + nutrition	Dispensary	Kinondoni	1,639	11
12. Mwenge	Standard	Dispensary	Kinondoni	1,597	5
13. Mbezi	Standard + nutrition	Dispensary	Kinondoni	870	11
14. Hananasif	Standard + nutrition	Dispensary	Kinondoni	530	7
15. Kigogo	Standard	Dispensary	Kinondoni	347	3
16. Mabibo	Standard + nutrition	Dispensary	Kinondoni	278	9
17. Goba	Standard	Dispensary	Kinondoni	177	4
18. Tabata	Standard	Health Centre	Ilala	2,193	10
19. Vingunguti	Standard + nutrition	Health Centre	Ilala	1,865	7
20. Kitunda	Standard + nutrition	Health Centre	Ilala	768	10
21. Pugu Kajiungeni	Standard	Dispensary	Ilala	561	11
22. Tabata NBC	Standard + nutrition	Dispensary	Ilala	249	10
23. Kinyerezi	Standard	Dispensary	Ilala	238	13
24. Mongolandege	Standard	Dispensary	Ilala	152	16
		Total:		33,191^b^	191
Standard of care					
1. Temeke	Standard + nutrition	Hospital	Temeke	17,409	3
2. Kigamboni	Standard	Health Centre	Temeke	2,879	9
3. Mbagala Round Table	Standard + nutrition	Dispensary	Temeke	850	5
4. Maji Matitu	Standard	Dispensary	Temeke	540	7
5. Kichemchem	Standard + nutrition	Dispensary	Temeke	211	3
6. Kingugi	Standard	Dispensary	Temeke	166	6
7. Sandali	Standard	Dispensary	Temeke	148	9
8. Kibada	Standard + nutrition	Dispensary	Temeke	109	8
9. Kisarawe II	Standard	Dispensary	Temeke	63	5
10. Magomeni	Standard + nutrition	Health Center	Kinondoni	2,361	8
11. Kimara	Standard	Dispensary	Kinondoni	2,270	5
12. Bunju	Standard + nutrition	Dispensary	Kinondoni	1,595	7
13. Kawe	Standard	Dispensary	Kinondoni	844	5
14. Kijitonyama	Standard + nutrition	Dispensary	Kinondoni	750	8
15. Kinondoni	Standard	Hospital	Kinondoni	396	5
16. Makuburi	Standard	Dispensary	Kinondoni	256	4
17. Ununio	Standard + nutrition	Dispensary	Kinondoni	115	6
18. Mnazi Mmoja Health Centre	Standard + nutrition	Health Centre	Ilala	3,650	4
19. Chanika	Standard	Health Centre	Ilala	1,413	12
20. Segerea	Standard	Health Centre	Ilala	678	8
21. Kiwalani	Standard + nutrition	Dispensary	Ilala	519	13
22. Gerezani	Standard	Dispensary	Ilala	350	2
23. Majohe	Standard + nutrition	Dispensary	Ilala	220	10
24. Mvuti	Standard + nutrition	Dispensary	Ilala	185	16
		Total:		37,977^b^	168

*Abbreviations*: *ART* antiretroviral therapy, *No*. number, *CHW* community health worker

^a^ Half of the clusters in each study arm were randomized to standard counseling and half to standard plus nutrition counseling.

^b^ This is *not* the expected number of participants as many ART patients do not live in the cluster (i.e., in the area surrounding the healthcare facility), and are therefore not eligible for this trial

For the purposes of randomization, clusters were first matched into pairs, separately within each municipality, based on the number of patients currently on ART at the facility. More specifically, the facility with the highest number of ART patients in Temeke was paired with the facility with the second highest number of ART patients in Temeke, and so on. The reason for this choice was that the intervention becomes more complex and thus plausibly less feasible to implement with an increasing volume of eligible participants. Most facilities only have one community outreach nurse. Thus, with an increasing number of eligible participants (for which ART patient volume is a proxy), the number of patients for whom the community outreach nurse has to supervise ART home delivery increases. An added benefit of matching on size prior to randomization is that it ensured an approximately equal number of participants in each study arm. The same process of matching facilities into pairs based on ART patient volume was used to randomize half of the facilities in each study arm to standard counseling and half to standard plus nutrition counseling (Fig. 1). The study design is thus a matched-pair cluster-randomized controlled 2x2 factorial trial. The randomization was conducted prior to the start of the study using computer-generated random numbers. For feasibility reasons, neither the research team nor the study participants are blinded to the intervention assignment.

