### Analysis plan

We will analyze the data by intention-to-treat analysis at the patient level in all primary analyses for this trial. The primary endpoint of this trial (i.e., the percentage of participants with a suppressed HIV viral load at the end of the study period) will be assessed by fitting robust clustered log-binomial models. Given the relatively small number of clusters in this trial, we cannot assume that randomization will eliminate confounding despite the matching of clusters described in the study design section. We will, therefore, adjust the analysis for viral load suppression at baseline. As viral load suppression is the outcome variable for the primary endpoint, adjusting for baseline viral load could be considered perfect adjustment for confounders. However, in secondary analyses, we will also adjust for other potentially confounding variables (e.g., participants’ socio-demographic characteristics) as a single baseline measurement may not account for trends in viral load suppression over time. Similarly, in secondary analyses, we will adjust for differing average exposure lengths to ART home delivery at each facility, and conduct subgroup analyses according to whether a participant received ART home delivery and by participants’ exposure length to ART home delivery.

Potential effect modification for any of the endpoints of this trial will be assessed through the likelihood ratio test. If statistically significant effect modification is present, we will present relevant results stratified by the effect modifier. All analyses will be conducted using Stata (Release 13; StataCorp, College Station, TX, USA).

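### Facilities were randomised in matched pairs within municipality on ART volume, but the stated primary model carries neither factor, so its interval may be somewhat wider than the design warrants

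*Protocol article*

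**What the plan says.** Under Randomization, "clusters were first matched into pairs, separately within each municipality, based on the number of patients currently on ART at the facility". The reason given for matching on volume is that "the intervention becomes more complex and thus plausibly less feasible to implement with an increasing volume of eligible participants"; balanced arm sizes are named as a further benefit. The section concludes: "The study design is thus a matched-pair cluster-randomized controlled 2x2 factorial trial". The abstract gives the count: "24 clusters were randomized to ART home delivery and 24 to the standard of care".

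Under Analysis plan, the primary endpoint "will be assessed by fitting robust clustered log-binomial models". The article defines a cluster as a facility with its catchment area, so the natural reading is a variance clustered on 48 facilities. The section refers to the matching and warns: "Given the relatively small number of clusters in this trial, we cannot assume that randomization will eliminate confounding". Its response is one covariate, baseline viral suppression. Other covariates, with socio-demographic characteristics as the example, are left to secondary analyses. Pair, municipality and ART volume are named in neither place.

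**The concern.** A design that pairs facilities on two factors makes the two facility results within a pair positively correlated whenever those factors predict the outcome. The arm difference is then more precise than for 48 unrelated facilities. A variance that treats the facilities as unmatched does not see this and reports too large a standard error. In a non-inferiority trial the confidence limit then lies further from the estimate than it should, and non-inferiority is harder to show.

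This is more than a detail left to a later document. The article raises both the matching and the small number of clusters, and then states a primary adjustment set that omits the factors used to randomise. At stake are the width of the primary interval and a choice best fixed in advance in an unblinded trial.

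**Working it through.** **1. Is the matching real?** Sorting Table 1 by ART volume within municipality and taking neighbours gives 9 pairs in Temeke, 8 in Kinondoni and 7 in Ilala: 9 + 8 + 7 = 24. Every pair has one facility in each arm (for example Temeke 17,409 and 15,663; Ilala 3,650 and 2,193). The arm totals, 33,191 and 37,977, agree with the table.

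**2. The plan's own power.** Inputs from Sample size: 700 per arm, 85% suppressed, 9-point margin, ICC 0.005 to 0.020, baseline-endline correlation 0.5, type I error 0.05 (taken as one-sided). Mean cluster size m = 700/24 = 29.17. The coefficient of variation (CV) of cluster size is not stated and is assumed.

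- Design effect = 1 + ((CV² + 1)m − 1) × ICC
- SE = √(2 × 0.85 × 0.15/700 × design effect), multiplied by √(1 − 0.5²) if credit is taken for baseline
- Power = Φ(0.09/SE − 1.645)

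At ICC 0.020 and CV 1 the design effect is 1 + 57.33 × 0.020 = 2.147, the SE is 0.0280 and power is 94%. With the baseline factor the SE is 0.0242 and power 98%. For CV up to 1.5 and ICC 0.005 to 0.020, power is 87-99.7% without baseline credit and at least 94% with it. At the extreme of CV 2.3 and ICC 0.020 it is 71% without and 81% with. The stated figure of at least 80% reproduces, and it takes no credit for matching.

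**3. Size of the SE error with no baseline term.** For equal clusters, the share of a facility mean's variance that lies between facilities is λ = m × ICC/(1 + (m − 1) × ICC). If a fraction s of the between-facility variance is shared within pairs, the within-pair correlation of facility means is ρ = λs. The unmatched SE is then too large by the factor 1/√(1 − ρ).

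| ICC | λ | Excess at s = 0.5 | Excess at s = 0.8 |
|---|---|---|---|
| 0.005 | 0.128 | 3% | 6% |
| 0.016 | 0.322 | 9% | 16% |
| 0.020 | 0.373 | 11% | 19% |

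Simulation with unequal clusters and no baseline term gave +4% to +19% for s from 0.5 to 0.8. One more extreme set had municipality and volume themselves drive the outcome, and took participant numbers as proportional to the square root of ART volume. At ICC 0.020 the excess there ran from 8% (s = 0.25) to 52% (s = 0.75).

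**4. The same with the planned baseline term.** The simulations assumed an individual baseline-endline correlation of about 0.5 and facility effects that fully persist. The facility-clustered SE was then only −2% to +4% off for s from 0.5 to 0.8. Baseline suppression takes up most of what pairing would have captured.

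**5. In points of suppression.** With the SE of 0.0242 from step 2, the one-sided half-width is 1.645 × 0.0242 = 4.0 points. A 4% excess is 4.0 − 4.0/1.04 ≈ 0.15 points. Without baseline, 1.645 × 0.0280 = 4.6 points, and a 19% excess is 4.6 − 4.6/1.19 ≈ 0.7 points. The margin is 9 points.

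**6. How the possible repairs behave.** All simulations used the risk-difference scale and a nominal one-sided 5%.

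- With nothing shared within pairs and size CV 1, the uncorrected facility-clustered sandwich gave 6-7% error. Clustering on pairs with t(23) alone gave 5.9-6.5%, so pairing does not cure this.
- Municipality plus log volume without a small-sample correction gave about 4-8%.
- Pair indicators with uncorrected facility-level clustering gave SEs about 30% too small and error of 12-15%.

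**The case against.** The strongest reply is that the planned model is not the one in which the mismatch looks large. It adjusts for baseline suppression, and with that term the SE error nearly vanishes if facility differences are stable. Nothing in the article shows that municipality or volume predicts suppression; volume was matched on for feasibility and balance. Analysing 24 pairs as unmatched is a usable choice, and it errs on the safe side for non-inferiority. All of this stands and limits the size of the point. It does not remove it: the persistence of facility effects is itself an assumption, and the article does not say that the match is broken on purpose.

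Four stronger readings are tempting, and the documents do not support them.

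- **Leaving out the pairs inflates false claims of non-inferiority.** The 6-7% error comes from a large-sample sandwich with unequal clusters, whether or not pairs are modelled. A small-sample reference is also detail that an unseen analysis plan may hold, so its absence is not a finding; it matters here only for the fix.
- **The trial is underpowered.** The stated power reproduces.
- **Using the matching is free precision.** Pair-level inference cuts the degrees of freedom from 46 to 23 and gains nothing if the factors explain nothing.
- **Follow-up length differs by municipality.** Study duration gives successive enrolment windows only, the timeline figure is not shown, and any such difference would not be between arms.

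**Conclusion.** The point holds in a limited form. The design is matched within municipality on ART volume, and the stated primary model uses neither factor. The consequence is a standard error that may be too large and an interval that may be conservative. The excess is nil to a few percent if baseline suppression absorbs lasting facility differences. It is roughly 5-20% without the baseline term, if half or more of the facility variance is shared within pairs. That shared fraction, the variation in cluster size and the persistence of facility effects are all assumptions; the documents give none of them. The simulations were on the risk-difference scale, not the log-binomial one. The estimate is not biased, and the claim of at least 80% power is not undermined. The change is worth making because it is cheap and the factors are already known, not because the conclusion is in danger.

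**What to change.** In the Analysis plan, add municipality (two indicators) and log ART volume (one term) to the primary model as pre-specified covariates beside baseline suppression. Use a small-sample-corrected cluster-robust variance with a t reference, since the uncorrected version runs above 5% when clusters are unequal. Report a pair-level analysis of the 24 within-pair differences, weighted by size, as a sensitivity check. Weighting matters: at size CV 1 an unweighted version had an SD of about 0.038, against 0.020 for the patient-level estimate. If the match is to be broken deliberately, say so and give the reason.

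Do not combine pair indicators with uncorrected facility-level clustering. Pair indicators can also put a log-binomial fit on its boundary. Under the assumed cluster sizes, the chance that at least one pair is fully suppressed is 18%, 55% and 98% at 85%, 90% and 95% suppression.

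The cost is a change of wording and about 3 degrees of freedom. If the factors explain nothing, the power loss runs from negligible to about 2 points; the upper end comes from pair-level variance (for example 91.0% to 89.3%).
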